**Table 2 Tab2:** Outcome evaluation

**Outcome**	**Tool**	**Description**	**Population**	**Timeline**
*Primary*				
Contact coverage	PHQ-9	PHQ-9 score > 4 as a proportion of those screened	Adult health centre attenders	Until we achieve target sample size
Effectiveness coverage	PHQ-9	Mean PHQ-9 score	Individuals who consent to receive HAP	3 months post recruitment
*Secondary*				
Sustained effectiveness	PHQ-9	Mean PHQ-9 score	Individuals who receive HAP	6 months post recruitment
Remission	PHQ-9	PHQ-9 score < 10	Individuals who receive HAP	3 and 6 months post recruitment
Response to treatment	PHQ-9	> 50% reduction in PHQ-9 score	Individuals who receive HAP	3 and 6 months post recruitment
Cost-effectiveness	(1) Inventory form for collecting system-level economic costs of delivering interventions (2a) Client Service Receipt Inventory form for collecting costs to patients (2b) Survey form for collecting costs of receiving HAP intervention to patients (3) WHODAS	(1) System-level costs: economic costs in WHO six building blocks for delivering the interventions (2a) Out-of-pocket costs for receiving general medical care and the related non-medical costs (e.g. time loss, travel) (2b) Out-of-pocket costs for receiving HAP intervention (e.g. time loss, travel) (3) Standardised disability scores used to estimate QALYs	(1) Finance records and individuals involved in delivery of the interventions (2a) Individuals who receive HAP (2b) Individuals who receive HAP (3) Individuals who receive HAP	(1) System-level costs: monthly, during the period of implementation (2a) Patient-level costs: 3 and 6 months post recruitment (2b) Patient level costs: 3 months post recruitment (3) 3 and 6 months post recruitment
Depression Awareness Questionnaire	Bespoke tool	Awareness about depression	Adult health centre attenders	Baseline and on randomly selected days at 6 and 12 months of implementation
Perceived social support	MSPSS	Perception of social support received	Individuals who receive HAP	3 and 6 months post-recruitment
	Bespoke tool			3 and 6 months post-recruitment
Treatment completion	Process data	Met treatment goals or completed the maximum number of sessions or were referred to mental health specialists	Individuals who receive HAP	Across the 12 months of implementation
Behavioural activation	PREMIUM Abbreviated Activation Scale	Patient-report activation levels	Individuals who receive HAP	3 and 6 months post-recruitment

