#### Effectiveness coverage outcome

Twenty-one participants with a PHQ-9 score ≥ 15 will be recruited from each of the 28 clusters (*N* = 588). Allowing for 20% of participants to be either not traceable by the outcome assessors or to not consent to participate at follow-up, we expect 17 participants from each cluster to complete the outcome evaluation at the three-month endpoint. This gives a sample size of 476 in which to assess our effectiveness coverage outcome at three months. This sample size provides 80% power to detect an effect size (standardised mean difference (SMD)) of 0.4 at the 5% significance level, assuming a coefficient of variation between clusters of 0.2. The assumptions underlying this calculation are based on the HAP trial for the effect size (i.e. a difference between the mean PHQ-9 scores of 11.9 [SD = 7.0] in the control arm and 8.9 [SD = 7.2] in the intervention arm) and the MANAS trial for the coefficient of variation (this trial tested a psychosocial intervention for common mental disorders in the same setting [32, 33]).

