#### Effectiveness coverage

The primary analyses will be intention-to-treat. Linear regression GEE will be used to compare mean PHQ-9 scores by arms, adjusting for within-facility clustering, baseline severity of depression and any confounding factors for which there is substantial imbalance between the arms at baseline. We will present an estimate of the effect size as an adjusted SMD and 95% confidence intervals and the intra-cluster correlation. For binary outcomes, the effect will be measured by the risk ratio (RR) and 95% confidence intervals using logistic regression models adjusted for within-facility clustering. Predefined effect-modification analyses will include adjustment for age, gender, marital status, education, employment status, and baseline PHQ-9 score. Finally, we will consider a sensitivity analysis to investigate the effect of missing data by using multiple imputation. We will not conduct an interim analysis as we do not anticipate any safety concerns related to the interventions.

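### Binary secondary outcomes are to be reported as risk ratios from logistic regression, a model that estimates odds ratios, and no step from one to the other is named

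*Protocol article*

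**What the plan says.** The sentence at issue is in the protocol article, Statistical methods {20a}, Effectiveness coverage: "For binary outcomes, the effect will be measured by the risk ratio (RR) and 95% confidence intervals using logistic regression models". The only qualification placed on the model concerns clustering: "using logistic regression models adjusted for within-facility clustering". No log link, standardisation, delta-method step or bootstrap step is mentioned.

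Table 2 lists the outcomes to which this applies. Remission is "PHQ-9 score < 10" and response is "> 50% reduction in PHQ-9 score", each at 3 and 6 months. Treatment completion is also yes or no. All three are listed as secondary.

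The article gives no expected rate for any of them. The nearest information is in Sample size {14}, Effectiveness coverage outcome, which takes from an earlier HAP trial "mean PHQ-9 scores of 11.9 [SD = 7.0] in the control arm and 8.9 [SD = 7.2] in the intervention arm".

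**The concern.** The sentence fixes both an effect measure and a model, and the model's direct output is a different measure. Exponentiating a logistic coefficient gives an OR, and the interval that comes with it is an interval for the OR. The two measures nearly agree when the event is rare. Remission and response are unlikely to be rare among people treated for depression, so the distinction matters here.

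An analyst who reads the sentence quickly could exponentiate the treatment coefficient and label it an RR. That would overstate any benefit in the published secondary results. An analyst who notices the mismatch has to choose a method that the article does not name. Different analysts could choose differently, and the choice might be made after the data are seen.

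**Working it through.** **The plan's own figure.** The article states no figure for a binary outcome. Its planning means can be checked through the power statement: "This sample size provides 80% power to detect an effect size (standardised mean difference (SMD)) of 0.4 at the 5% significance level", with 17 completers in each of 14 clusters per arm and a between-cluster coefficient of variation k = 0.2. The standard formula for comparing means in a cluster trial is

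c = 1 + (1.96 + 0.84)² × [(s₁² + s₀²)/m + k²(μ₁² + μ₀²)] / (μ₁ − μ₀)².

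- Individual-level term: (7.2² + 7.0²)/17 = 100.84/17 = 5.93.
- Cluster-level term: 0.04 × (8.9² + 11.9²) = 0.04 × 220.82 = 8.83.
- c = 1 + 7.85 × 14.76/9 = 13.9 clusters per arm. With 14 per arm the power is 80.4%, so the stated 80% is reproduced.

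The means and SDs are therefore the real planning inputs, and they are the only basis in the article for a remission rate.

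**How far the OR lies from the RR.** With p₀ and p₁ the proportions in the Facility and Community arms:

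- RR = p₁/p₀
- OR = p₁(1 − p₀)/[p₀(1 − p₁)] = RR × (1 − p₀)/(1 − p₁)

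Whenever p₁ > p₀, the OR exceeds the RR by the factor (1 − p₀)/(1 − p₁).

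**Illustration 1: assumed rates, 10-point gain.**

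| p₀ | p₁ | RR | OR |
|---|---|---|---|
| 0.30 | 0.40 | 1.33 | 1.56 |
| 0.40 | 0.50 | 1.25 | 1.50 |
| 0.50 | 0.60 | 1.20 | 1.50 |
| 0.60 | 0.70 | 1.17 | 1.56 |

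With a 5-point gain over the same control rates, RR runs from 1.08 to 1.17 and OR from 1.22 to 1.26.

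**Illustration 2: normal approximation to the planning means.** Remission is taken as a score below 9.5, since scores are whole numbers.

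- Control: Φ((9.5 − 11.9)/7.0) = Φ(−0.343) = 0.366.
- HAP: Φ((9.5 − 8.9)/7.2) = Φ(0.083) = 0.533.
- RR = 0.533/0.366 = 1.46. OR = 1.46 × 0.634/0.467 = 1.98.

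Moving the cut-point between 9 and 10 gives RR 1.43 to 1.49 and OR 1.97 to 1.99.

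**Illustration 3: both arms receive HAP.** Here the comparator is placed at the HAP-arm mean of 8.9, and the planned SMD of 0.4 is applied with a pooled SD of 7.1. The Community mean is then 8.9 − 0.4 × 7.1 = 6.06. Remission is 53.3% against 68.4%, which gives RR 1.28 and OR 1.89.

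**Check on fitted models.** The rates in illustration 2 correspond to about 87 and 127 remissions out of 238 per arm. Unadjusted fits that ignore clustering gave:

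- exponentiated logistic coefficient: 1.99
- marginal standardisation of the same logistic model: RR 1.46
- Poisson model with log link and robust variance: RR 1.46

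The logistic model can therefore yield the RR, but only through a further step.

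**The case against.** The strongest reply is that the sentence can be carried out as written. Marginal standardisation of a logistic model gives a valid RR, so measure and model are compatible, and only the conversion and its interval are missing. Statistical methods {20a} promises a detailed analysis plan before any analysis. That plan is not shown and may supply the step. This stands in part. A reader might infer that the trial will publish ORs labelled as RRs, but nothing in the article says so; it is a risk and not the only outcome. What remains is that the article itself chose both the measure and the model, and the pair does not match without a step that it does not name.

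A second reply concerns size, and it also stands. A reader might take 37% against 53% as the trial's expected remission rates. The article states none. The figures come from an earlier contrast of HAP with control, whereas here both arms receive HAP (sections {6b} and {16c}). Normality is also rough: a mean of 8.9 with SD 7.2 puts about 11% of scores below zero, which the PHQ-9 cannot take. The figures are illustrations. The direction does not depend on them.

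A third reply is that little rests on this: the outcomes are secondary, and the choice of scale would not ordinarily change the test of no effect. That is correct, and it limits the weight of the point. The reported size of effect is still what readers will use.

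**Conclusion.** The mismatch is real and is confined to the binary secondary outcomes. If an exponentiated logistic coefficient were reported as the RR, the apparent relative gain would be inflated. With assumed control rates of 30% to 60% and a 10-point gain, it would be 50% to 56% in place of 17% to 33%. On the planning means it would be 98% in place of 46%, about double. These sizes rest on assumed rates or on a normal approximation to another trial's contrast. That the OR exceeds the RR when the intervention helps rests on neither.

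Two wider readings are not supported. The effectiveness primary outcome, mean PHQ-9 by linear GEE with an adjusted SMD, is untouched. A reader might also extend the point to contact coverage, which uses logistic regression too. That section names no RR, so it contains no mismatch, and at the planned 11% against 14% the two measures nearly agree (RR 0.14/0.11 = 1.27, OR 1.32).

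The point should be corrected, but it does not threaten the trial's main conclusions.

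**What to change.** Amend the sentence, and carry the same wording into the analysis plan, in one of two ways:

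1. Replace the logistic model with a log-link GEE clustered on the randomised cluster: modified Poisson with robust variance, or log-binomial. The exponentiated coefficient is then the RR.
2. Keep the logistic model and state that the RR and its 95% interval come from marginal standardisation, with inference at cluster level, for example by resampling whole clusters.

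The cost is one sentence, with no new data, no change in sample size and no new software. It should be settled before the analysis begins.

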## Statistical methods

### Statistical methods for primary and secondary outcomes {20a}

A detailed analysis plan will be agreed with the data safety and monitoring board towards the end of the trial and before any analysis is undertaken. Findings will be reported as per the CONSORT guidelines for CRTs. Baseline comparability will be assessed for participants who could and could not complete outcome assessments. Comparability of the two intervention arms will be assessed for potential confounding factors such as age, gender, education, and severity of depression at baseline.

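### The binary-outcome models list no adjustment for baseline PHQ-9, so a systematic difference in entry severity would bias the remission comparison

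*Protocol article*

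**What the plan says.** The Effectiveness coverage paragraph of the statistical methods names adjustment terms separately for two kinds of outcome.

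- **Mean PHQ-9 (linear GEE):** "adjusting for within-facility clustering, baseline severity of depression and any confounding factors for which there is substantial imbalance between the arms at baseline".
- **Binary outcomes (risk ratio with 95% confidence interval):** "using logistic regression models adjusted for within-facility clustering".

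Baseline PHQ-9 appears once more in that paragraph, for a different purpose: "Predefined effect-modification analyses will include adjustment for age, gender, marital status, education, employment status, and baseline PHQ-9 score".

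The opening of section {20a} plans an arm comparison on "potential confounding factors such as age, gender, education, and severity of depression at baseline", so baseline severity is recognised as a possible confounder. It also says: "A detailed analysis plan will be agreed with the data safety and monitoring board towards the end of the trial".

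Table 2 defines remission as "PHQ-9 score < 10" and response as a reduction of more than half from the participant's own starting score, both at 3 and 6 months. These outcomes serve secondary hypotheses 2b and 2c.

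**The concern.** Remission and response are derived from the same questionnaire, in the same people, as the mean PHQ-9 outcome. Entry requires a score of at least 15, so participants start between 15 and 27. Someone who enters at 25 must fall 16 points to reach 9 and count as remitted; someone who enters at 15 must fall 6.

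Three features of the design make a systematic severity difference between arms plausible:

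- Clusters were randomised before the first participant was recruited (Sequence generation {16a}).
- Case managers do the enrolling (Implementation {16c}) and are listed as unblinded (Who will be blinded {17a}).
- In the Community Model only, the volunteers identify people with possible depression and help them reach the health centre (Intervention description {11a}). Hypothesis 1a expects this to raise demand, so it may also change who presents.

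If entry severity does differ, the mean PHQ-9 result would be corrected for it and the remission result, analysed as written, would not. The two could then disagree because of case-mix alone.

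**Working it through.** **1. The plan's own figure.** For the effectiveness outcome the protocol states 80% power with 14 clusters per arm, 17 completers per cluster, means 11.9 (SD 7.0) and 8.9 (SD 7.2), and a between-cluster coefficient of variation of 0.2. Using the usual cluster-trial formula for two means (two-sided 5% assumed):

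- V = [(7.0² + 7.2²)/17 + 0.2² × (11.9² + 8.9²)] / (11.9 − 8.9)² = (5.93 + 8.83)/9 = 1.64
- power = Φ(√((14 − 1)/1.64) − 1.96) = Φ(0.855) = 80.4%

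The stated power reproduces, and nothing below alters it.

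**2. Inputs for the bias.**

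- From the protocol: control mean 11.9 and an SD of about 7.1 at follow-up; 28 × 17 = 476 completers.
- Assumed, because the protocol gives no values: baseline SD 3 among those scoring at least 15, ICC 0.05, correlation r between baseline and 3-month score of 0.2 to 0.5, and a baseline gap of 1 point.

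**3. Remission, by hand.** The score is an integer, so remission means falling below 9.5 on a continuous scale.

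- Normal density at 9.5 with mean 11.9 and SD 7.1: about 0.053 per point.
- Slope of follow-up on baseline: r × 7.1/3 = 0.47, 0.71 and 1.18 at r = 0.2, 0.3 and 0.5.
- Shift in remission for a 1-point gap = 0.053 × slope: about 2.5, 3.8 and 6.3 percentage points.

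A simulation of 3,000 null trials per scenario gave 2.6, 3.5 and 6.5 points, with remission lower in the arm that starts more severe. With baseline PHQ-9 in the model the bias was about 0. The shift is close to proportional to the gap, so half a point gives about half as much.

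**4. Remission and response on the risk-ratio scale.** This is a large-sample calculation with scores rounded and baseline limited to 15–27 (baseline SD about 2.6), no true effect, the Community arm about 0.9 points more severe, and no baseline adjustment:

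| r | Remission RR | Response RR |
|---|---|---|
| 0 | 1.00 | 1.07 |
| 0.1 | 0.97 | 1.04 |
| 0.2 | 0.94 | 1.00 |
| 0.3 | 0.91 | 0.97 |
| 0.5 | 0.85 | 0.90 |

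Response behaves differently because its threshold moves with the participant. It depends on follow-up minus half of baseline, and a gap d moves the mean of that quantity by (slope − 0.5) × d. The distortion vanishes when the slope is about 0.5 (r about 0.2) and changes sign on either side.

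**5. Effect of adjusting.** In a GEE simulation with 28 clusters of 17, r = 0.3 and a gap of about 1 point (250 runs), adding baseline PHQ-9 moved the null remission RR from 0.89 to 1.00, the response RR from 0.96 to 1.00, and the mean PHQ-9 difference from 0.73 to 0.03.

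**6. Chance imbalance and error rate.** The standard error of the baseline difference is 3 × √(2 × (1 + 16 × 0.05)/238) = 0.37 points, so a 1-point gap is about 2.7 standard errors and would mostly reflect case-mix. Rejection rates of an unadjusted cluster-level test on remission with no true effect:

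| Systematic gap (points) | r = 0.2 | r = 0.3 | r = 0.5 |
|---|---|---|---|
| 0 (chance only) | 5.0% | 4.8% | 5.4% |
| 0.37 | 5.0% | 5.5% | 7.1% |
| 0.5 | 5.8% | 5.9% | 8.5% |
| 1 | 8% | 9% | 21% |

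With baseline in the model, the error at a 1-point gap was 4–5%.

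**7. Precision.** Without imbalance, adjustment adds about 1 power point at r = 0.2 to 0.3 and about 3 at r = 0.5.

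**The case against.** The strongest reply is that this is a condensed article, that a detailed analysis plan is still to be agreed before any analysis, and that covariates for secondary models are commonly left to such a plan. The binary sentence does not say that clustering is the sole adjustment, and the planned baseline comparison is not tied to one outcome. This stands in part: a reader might infer that the protocol rules out baseline adjustment for binary outcomes, and it does not. But the article does not stay silent on covariates. It names adjustment terms for both kinds of model in the same paragraph, and baseline severity is in one list and absent from the other, with no reason given.

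Four stronger readings are also tempting, and the documents do not support them:

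- **Any severity difference biases the result.** Chance imbalance after cluster randomisation adds error in a given trial but no bias in expectation, and it leaves the unconditional 5% level intact. Bias needs a systematic difference in who is enrolled.
- **Response is affected as remission is.** It is already scaled to baseline; its distortion is smaller, is near nil at a slope of about 0.5, and reverses direction.
- **The binary tests lose their 5% level, up to 21%.** That figure needs both a 1-point systematic gap and a correlation of 0.5. Both are assumed, and the correlation is high for a sample restricted to scores of at least 15.
- **The mean PHQ-9 analysis is fully protected.** It is protected against measured severity and against whichever confounders are adjusted for, not against other differences in who is recruited.

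**Conclusion.** The point holds in a limited form. As written, the binary-outcome models carry no baseline severity term while the mean PHQ-9 model does, and the design makes a systematic severity difference plausible. For remission, an assumed 1-point gap under no true effect produces a spurious difference of roughly 2.5 to 6.5 percentage points at correlations of 0.2 to 0.5. Smaller gaps do proportionally less, and no gap does nothing in expectation. For response the direction cannot be predicted without knowing the slope, so it could not be reasoned away afterwards.

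The size rests on assumed values for the baseline SD, ICC, correlation and gap. The case for adjustment rests on bias more than on power. It concerns secondary outcomes, and worth correcting is a fair description of its weight.

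**What to change.** In the Effectiveness coverage paragraph, and in the detailed analysis plan, state that the remission and response models include continuous baseline PHQ-9, as the mean PHQ-9 model does. State also that the risk ratio is obtained from the adjusted model, for example by standardising predicted risks over the observed baseline distribution. That settles how a logistic model yields a risk ratio, which the paragraph leaves open; another valid route to an adjusted risk ratio would serve equally well.

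The cost is about one sentence. The covariate is the eligibility score, so it is held for every enrolled participant and needs no new data collection. Because the analysis plan is to be agreed before any analysis, the change can be made without reference to results.

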#### Economic evaluation

This will be based on the estimation of the actual costs of delivery of the Facility and Community Models and costs incurred by individual participants, as described in Table 2. To generate incremental costs of the two models, we will use multi-level generalised linear models (and controlling for clustering effects for skewed cost data) at the individual patient-level analysis. Costs per patient will be the outcome variable and one dummy variable indicating the two models (with the Facility Model as the reference) will be the exposure variable. Other covariates include time and interaction terms between intervention dummies and time. To provide mean and 95% confidence intervals (CIs) for the estimated incremental costs, we will use bootstrapping. The same strategy can be applied to incremental effectiveness and incremental cost-effectiveness ratios (ICERs) for generating their means and 95% CIs. We will generate cost-effectiveness acceptability curves with different levels of thresholds on willingness to pay, from either health system perspective or societal perspective, to show the probability that the intervention remains cost-effective as thresholds change. We will also specifically examine the extent to which the interventions impact on out-of-pocket expenditure for health care, one of the leading causes of health-related impoverishment for people with depression. We will assess the long-term financial sustainability of the scaled-up Community Model by estimating the costs of implementation of the Community Model (which includes the HAP) at the national level. We will estimate the fiscal capacity for scaling up the model at a regional and national level.

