**Methods:**

A hybrid type 2 effectiveness implementation cluster randomised controlled trial will be implemented in the state of Goa, India. Twenty-eight clusters of villages and their associated public sector health centres will be randomly allocated through restricted randomisation. Clusters will be randomly allocated to the ‘Community Model’ or ‘Facility Model’ arms. All clusters will offer the HAP and clusters in the ‘Community Model’ arm will additionally receive activities delivered by community volunteers (“*Sangathis”*) to increase awareness about depression and support demand for and adherence to HAP. The primary outcomes are Contact Coverage (Patient Health Questionnaire [PHQ-9] score > 4 as a proportion of those screened) and Effectiveness Coverage (mean PHQ-9 score amongst those who score ≥ 15 at baseline, i.e. those who have moderately severe to severe depression) at 3 months post-recruitment. Additional outcomes at 3 and 6 months will assess sustained effectiveness, remission, response to treatment, depression awareness, social support, treatment completion, and activation levels. Economic and disability outcomes will be assessed to estimate incremental cost-effectiveness ratios. Implementation will be evaluated through process data and qualitative data informed by the RE-AIM framework. A minimum of 79488 primary care attenders will be screened for the Contact Coverage outcome, and 588 individuals with PHQ-9 ≥ 15 will be recruited for the Effectiveness Coverage outcome.

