#### Effectiveness and cost-effectiveness of the integrated intervention

Individual level outcome data will be collected at 3 months and 6 months post-recruitment for those eligible for the effectiveness coverage outcome. The second primary outcome will be mean PHQ-9 score at 3 months post recruitment. The primary endpoint for effectiveness of the integrated intervention is 3 months post recruitment, as we would expect the optimal effect of HAP at that timepoint. The 6-month endpoint is included to evaluate the sustainability of the effect of HAP.

The outcome assessment measures are summarised in Table 2. Depression awareness will be measured using a bespoke tool designed based on the content of the community intervention. The tool will be administered to a consecutive sample of 40 attenders at all the health centres on randomly selected days at baseline and at 6 and 12 months of implementation. Out-of-pocket costs for receiving care, and related non-medical costs, will be collected using a survey tool developed for the purpose which incorporates the Client Service Receipt Inventory (CSRI), a tool that has been used extensively in the study setting [15, 16, 20]. Out-of-pocket costs for receiving HAP intervention (e.g. time loss, travel) will be measured using a survey tool. Standardised disability scores used to estimate quality-adjusted life years (QALYs) will be collected using the WHO Disability Assessment Schedule 2.0 (WHODAS 2.0), which has also been used extensively in this and other settings [16, 21]. The WHODAS assesses behavioural limitations and restrictions related to an individual’s participation, independent from a medical diagnosis [22]. Perceived social support will be measured using a bespoke tool and the Multidimensional Scale of Perceived Social Support (MSPSS) a 12-item instrument designed to measure an individual’s perception of support from family, friends, and a significant other [23]. MSPSS has been widely used and validated in the study setting [24–26]. Additionally, perceived social support related to *Sangathis* will be measured using a bespoke tool. The PREMIUM Abbreviated Activation Scale (PAAS) is a five-item scale, originally developed and used in the trial of the HAP [15, 16] and is based on the Behavioural Activation for Depression Scale (BADS) [27]. It includes five self-reported indicators of behavioural activation such as engagement with a variety of activities and associated pleasure and mastery.

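### A bootstrap mean and 95% CI of the ICER is unstable, and can be uninterpretable, if the QALY difference is close to zero

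*Protocol article*

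**What the plan says.** Three sentences in the Economic evaluation section (Statistical methods {20a}) matter here.

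- For costs the plan is firm: "To provide mean and 95% confidence intervals (CIs) for the estimated incremental costs, we will use bootstrapping".
- It then allows the same method, in permissive terms, for "incremental effectiveness and incremental cost-effectiveness ratios (ICERs) for generating their means and 95% CIs".
- It also commits to a second summary of uncertainty: "We will generate cost-effectiveness acceptability curves with different levels of thresholds on willingness to pay".

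The denominator of the ratio is described under Outcomes {12}: "Standardised disability scores used to estimate quality-adjusted life years (QALYs) will be collected", using WHODAS 2.0. Table 2 places those follow-up measurements at 3 and 6 months. The contrast between arms is HAP plus community support against HAP alone: "All clusters will offer the HAP and clusters in the ‘Community Model’ arm will additionally receive activities".

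The article does not say whether the point ICER is the ratio of the two mean differences or the average of replicate ratios. It gives no rule for replicates in which the QALY difference is zero or negative.

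**The concern.** A bootstrap mean and interval are sensible for a difference in cost or a difference in QALYs. The ratio behaves differently, in two ways.

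1. **The mean.** When some replicate QALY differences fall close to zero, the replicate ICERs have very heavy tails. Their average is then driven by a few extreme values, changes with the seed, and need not resemble mean incremental cost divided by mean incremental effect.
2. **The ordering.** A negative ICER can mean cheaper and better, or dearer and worse. A positive ICER can mean dearer and better, or cheaper and worse. Percentile limits require the replicates to be sorted, and once the denominator changes sign the sorted order no longer runs from favourable to unfavourable.

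Cost-effectiveness is one of the stated objectives, and the Discussion names policymakers as the audience. A headline ICER that depends on the seed, or an interval whose lower limit looks like a saving but comes from replicates that are dearer and worse, would be hard to defend.

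**Working it through.** **Step 1. The plan's own precision.** The article gives no cost, QALY or ICER figure to reproduce. The nearest design signal is the power for the effectiveness outcome (Sample size {14}).

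Inputs: 14 clusters per arm; 17 participants per cluster after the 20% loss; means (SD) of 11.9 (7.0) and 8.9 (7.2); between-cluster coefficient of variation 0.2; two-sided 5% (sidedness is not stated).

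- Variance term: (7.0² + 7.2²)/17 + 0.2² × (11.9² + 8.9²) = 5.93 + 8.83 = 14.77.
- Power: Φ(√[(14 − 1) × 3.0² / 14.77] − 1.96) = Φ(2.815 − 1.96) = 80.4%. The stated figure is 80%, so it reproduces.

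**Step 2. How often replicates would cross zero.** Assume QALYs are measured with the precision that gives 80% power at an SMD of 0.4. The SE of the SMD is then 0.4/(1.96 + 0.84) = 0.143, and the share of replicates at or below zero is Φ(−SMD/0.143).

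| Standardised QALY effect | Distance from zero | Replicates ≤ 0 |
|---|---|---|
| 0.1 | 0.70 SE | 24% |
| 0.2 | 1.40 SE | 8% |
| 0.3 | 2.10 SE | 2% |
| 0.4 | 2.80 SE | 0.3% |

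The 0.4 comes from the HAP trial's control-versus-intervention contrast. It does not come from adding community support to HAP, so a smaller incremental effect is credible.

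**Step 3. Behaviour of the bootstrapped ICER.** Incremental cost and incremental effect were drawn as independent normals, each in units of its own SE. Cost was fixed at 3 SE and effect varied. Each bootstrap had 1,000 replicates and was repeated 2,000 times with new seeds. The third column gives the 2.5th to 97.5th centile of the replicate mean over those repeats. The last column but one gives the median percentile limits.

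| QALY difference | Point ICER | Replicate mean across seeds | Percentile interval | Replicates ≤ 0 |
|---|---|---|---|---|
| 0.5 SE | 6.0 | −51 to +40 | −40 to +42 | 31% |
| 1 SE | 3.0 | −21 to +27 | −27 to +30 | 16% |
| 1.96 SE | 1.53 | −4.5 to +7.8 | −0.1 to 9.6 | 2.5% |
| 2.8 SE | 1.07 | 0.35 to 2.2 | 0.32 to 3.65 | 0.3% |
| 4 SE | 0.75 | 0.78 to 0.85 | 0.25 to 1.72 | 0.0% |

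Within each row the estimates are the same and only the seed changes. At 2.8 SE the interval is positive and ordered, but the mean still moves with the seed. At 4 SE both are stable, and the replicate mean sits only slightly above the ratio of means.

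**Step 4. The ordering problem** (illustrative cost and QALY differences).

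- (+100, +0.01) and (−100, −0.01) both give +10,000.
- (+100, −0.01), which is dominated, and (−100, +0.01), which is dominant, both give −10,000.
- Making the dominated case worse, (+100, −0.05), moves its ICER to −2,000, nearer zero.

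In Step 3, with cost at 3 SE, only Φ(−3) = 0.1% of replicates are cost-saving. The negative limits there come almost wholly from dominated replicates, yet they sort below every dearer-and-better replicate.

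**Step 5. The alternative on the same inputs.** Take the 1 SE row and a threshold λ = 3 in the same units. Incremental net benefit is λ × effect − cost = 3 × 1 − 3 = 0. Its SE is √(3² × 1² + 1²) = 3.16, so the 95% CI is about −6.2 to 6.2. With 1,000 replicates the Monte Carlo error of the mean is about 1.96 × 3.16/√1,000 = ±0.2. The replicate-mean ICER from the same inputs ranges over −21 to +27.

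**The case against.** **The wording is permissive.** The plan commits to bootstrapping for costs but only allows it for ICERs. A reader might infer that the trial will certainly report an average of replicate ratios; the text does not go that far. What stands is that this is the only uncertainty summary the article names for the ICER itself, and that it speaks of a mean of the ICER.

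**A valid summary is already planned.** At each threshold an acceptability curve gives the probability that net benefit is positive, so sign and quadrant are handled correctly. This stands in full. A reader might infer that the whole cost-effectiveness conclusion is unreliable, and the document does not support that.

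**The interval is not generally invalid.** In the same simulation framework the percentile interval covered the true ratio in 94% to 98% of runs. It would be wrong to say that it badly undercovers, or that a ratio can never be bootstrapped. The fault is in interpretation across quadrants and in the unstable mean.

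**It may never arise.** If the QALY difference turns out to be about 4 SE from zero, the instability is absent. This also stands, but the method has to be fixed before the difference is known.

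**Clustering.** A reader might infer that the bootstrap ignores clusters. The section specifies multi-level cost models that control for clustering and does not state the resampling unit. An article may leave that to the analysis plan, and it is no part of this point.

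**Conclusion.** The concern holds in a limited and conditional form. If the QALY difference is within about 2 to 3 SE of zero, the mean of bootstrapped ICERs depends on the seed. Where replicates cross zero, the percentile interval also combines results with opposite meanings. At a borderline-significant QALY difference (1.96 SE) the replicate mean ranges from −4.5 to +7.8 around a point ICER of 1.53. At the signal matching 80% power (2.8 SE) only the mean is still noticeably unstable.

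The sizes rest on assumptions: independent normal differences, a cost difference of 3 SE, and, for Step 2, QALY precision equal to that of PHQ-9. The document supplies no cost or QALY figures to replace them. The defect is confined to one reporting format for a secondary outcome. It does not touch the primary analyses, the sample size, the data collected or the acceptability curves.

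**What to change.** In the Economic evaluation section, make two changes.

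1. Define the ICER as mean incremental cost divided by mean incremental effect.
2. Replace the bootstrap mean and CI of the ICER with incremental net monetary benefit and its 95% CI, at the willingness-to-pay thresholds used for the acceptability curves and from the same bootstrap replicates.

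The bootstrap for incremental costs and incremental effectiveness, and the acceptability curves, can stay as written. The cost is a change of wording: no new data and no additional resampling are needed.
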